## Abstract

**Background and rationale:**

Idiopathic pulmonary fibrosis is a critical disease with a poor prognosis. Although different studies have been conducted for the treatment of idiopathic pulmonary fibrosis, limited treatments are available. Jin-shui Huan-xian granule (JHG), which is a Chinese medicine herbal compound, has shown promising efficacy in reducing frequencies of acute exacerbations, improving exercise capacity the quality of life of patients with idiopathic pulmonary fibrosis. This study is to evaluate the efficacy and safety of JHG for IPF.

**Subjects and methods:**

This is a multicenter, randomized, double-blind, placebo-controlled clinical trial. A total of 312 idiopathic pulmonary fibrosis patients will be enrolled and randomly allocated to one of the two groups with 1:1. After a 2-week washout period, 52-week treatment will also be performed for all the patients. Patients in the experimental group and the control group will be given JHG and JHG placebo, respectively. Outcome measures including acute exacerbations, pulmonary function, dyspnea, exercise capacity, and quality of life will be evaluated in this study.

**Discussion:**

Based on our previous study, it is hypothesized that JHG will reduce acute exacerbations; improve exercise capacity, pulmonary function, and quality of life; and delay the disease progression-free. High-level evidence-based support for TCM in IPF will also be obtained in this study.

**Trial registration:**

ClinicalTrials.gov NCT04187690. Register on December 11, 2019

## Introduction

Idiopathic pulmonary fibrosis (IPF) is a progressive interstitial lung disease with poor prognosis and short median survival [1]. The etiology remains not completely clear [2]. With a low prevalence rate, some scholars consider it as a rare disease [3]. In China, it has also been included in the list of rare diseases in 2018. However, different studies show that it has been more common in recent years [4, 5]. After diagnosis, IPF patients will follow a median survival of 2–5 years [5]. Data also shows that IPF patients in Sweden will spend an annual average of $13,975 for hospitalization [6]. In America, a total of 2 billion dollars has been spent on the prevention and treatment of IPF every year [7]. IPF has caused a heavy socio-economic burden.

Although different studies have been performed in recent years, the available treatments remain limited. As reported in the latest international guidelines for IPF, only pirfenidone and nintedanib are recommended in clinical application [8]. They could improve pulmonary function, quality of life, and exercise capacity and delay the disease progression for IPF patients [9–11]. However, the related side effects have also been reported. One study showed that a total of more than 10% of IPF patients taking pirfenidone or nintedanib have discontinued medication permanently due to side effects [12], and their long-term effects are still under debate. Up to now, evidences for other drugs are still insufficient [13–20]. Limited researches have also been performed on non-drug treatment for IPF [21]. However, the levels of the available evidences are also low. It is urgent to conduct further researches on the treatments of IPF [22].

Traditional Chinese medicine (TCM) has different treatments and certain efficacy for respiratory diseases. Chinese herbal medicine (CHM) is the most used measures. According to TCM theory and our previous studies, IPF should be treated according to *feiwei* or *feibi*, and the core TCM pathogenesis includes vital *qi* deficiency, lung collaterals obstruction, phlegm and blood stasis, and accumulation of damage. We have also developed a TCM therapeutic scheme for IPF based on the above studies. Then, the CHM formulation has been optimized to Jin-shui Huan-xian granule (JHG) by clinical application and basic experiments.

JHG is a Chinese medicine compound. Our previous study shows it has a potential treatment effect by inhibiting the differentiation of fibroblasts into myofibroblasts in a pulmonary fibrosis mouse model [23]. We have also performed an exploratory trial to assess the efficacy and safety for IPF patients. The results show that JHG could reduce the frequencies of acute exacerbation and improve lung function and exercise capacity with a reliable safety for IPF patients (to be published). To obtain high-level evidence-based supports, we will conduct a randomized controlled trial to confirm the efficacy and safety of the Jin-shui Huan granule for IPF.

The following contents will be paid attention to in our study: (1) to assess JHG in reducing AEs and improving exercise capacity for IPF, (2) to evaluate the JHG in improving clinical symptoms and quality of life, and (3) safety of JHG will also be assessed.

## Methods/design

### Study design

This is a multicenter, randomized, double-blind, placebo-controlled clinical trial. The efficacy and safety of JHG for IPF will be assessed in this study. We will recruit 312 stable IPF patients and randomly assign them into the experimental group or the control group with a ratio of 1:1 after a wash-out period of 2 weeks. Then, all the enrolled patients will be given a 52-week treatment of JHG or placebo. The outcomes assessed in this study include frequencies of acute exacerbations, exercise capacity, proportion of progression-free patients, lung function, all-cause mortality, clinical symptoms and signs, dyspnea, health-related quality of life (HRQoL), and adverse events. The protocol follows the Standard Protocol Items for Clinical Trials with Traditional Chinese Medicine 2018: Recommendations, Explanation and Elaboration (SPIRIT-TCM Extension 2018) [24]. The study will also be conducted in accordance with the Declaration of Helsinki (as revised in 2013). The whole study flow chart is found in Fig. 1.

**Fig. 1 Fig1:**
[figure not shown]
The whole flow chart for this study

### Patients’ eligibility and criteria

#### Diagnosis criteria of IPF

The diagnosis of IPF will be performed referring to the classification and diagnosis standard of idiopathic interstitial pneumonia published by the American Thoracic Society and European Respiratory Society in 2018 [25]: (1) patients with any other known causes of interstitial lung disease (ILD), such as occupational environment exposure, connective tissue disease, or drugs, should be excluded; (2) for the patients without surgical lung biopsy, high-resolution CT (HRCT) should show a representation of usual interstitial pneumonia (UIP); (3) a specific combination of HRCT and lung biopsy histopathological results should be met for the patients with a surgical lung biopsy; and (4) if necessary, a multi-disciplinary discussion would also be adopted for difficult cases.

#### Diagnostic criteria of TCM syndromes

Because of that, there is a lack of diagnostic criteria for TCM syndromes for IPF; now, the differentiation of TCM syndromes will be referred to the *Diagnostic criteria of TCM syndromes for diffuse interstitial lung disease* [26]. Two independent TCM researchers will perform the syndrome differentiation blindly. If any disagreement appears, the third researcher will be consulted, and a consensus will be reached. The core TCM pathogenesis, which is the accumulation and damage of collaterals due to deficiency of vital qi, will also be taken into account [27]. So, IPF patients with TCM syndromes including lung qi deficiency, lung-kidney qi deficiency, and yin deficiency and inner heat will also be enrolled in this study.

#### Inclusion criteria

Any participant should meet all of the following criteria: (1) meeting the diagnostic criteria of IPF; (2) with ages between 40 and 85 years old; (3) meet the criteria of TCM syndrome differentiation: patterns of lung qi deficiency, lung-kidney qi deficiency, and yin deficiency and inner heat [16]; (4) not participating in any other interventional trial within the previous one month before enrollment; and (5) signing the informed consent form.

#### Exclusion criteria

The patients meeting any of the following criteria will be excluded: (1) pregnant and breastfeeding women or patients with a recent pregnancy plan; (2) delirious, dementia, or with any mental disorder; (3) complicated with severe cardiac insufficiency, liver and kidney diseases, bronchial asthma, chronic obstructive pulmonary disease, tumor, or thoracic deformity; (4) with a condition of limb dysfunction or bedridden; and (5) known to be allergic to any component of the therapeutic drugs.

#### Drop-out criteria

Drop-out criteria have been set up as follows: (1) not willing to continue the trial with any reason and may induce the incompleteness of study data, (2) should not continue to participate in the trial due to allergy or serious adverse events, and (3) patients who are no longer taking the given medication and physical examination and lost in the visit.

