### Procedures and interventions

Patients in the experimental group will be treated with JHG for 52 weeks, while the control group are treated with a JHG placebo. JHG is a Chinese herbal compound medicine. The compounds of one dosage for JHG are found in Table 1. The placebo used in this study will contain 5% of the same components of JHG. All the JHG and placebo will be produced and packed by Jiang Yin Tian Jiang Pharmaceutical Co. Ltd., Jiangsu, People’s Republic of China, without any difference in the appearance, color, smell, and weight. The drug quality will be tested by the organization with specific qualifications before application and consistent with the required quality standards. Each dosage of JHG granules or placebo has been produced and packed into 4 bags with 10.9 g per bag (Batch number: 2006337). JHG or JHG placebo will be prescribed 2 bags each time, twice a day orally with 5 days on and 2 days off.

**Table 1 Tab1:** Components of Jin-shui Huan-xian granules

Chinese name	Latin name	Parts of the substances	Amount (g)
Ren Shen	*Radix Ginseng*	Root	6
Shu Di Huang	*Rehm,annia glutinosa Libosch*	Root tuber	12
Mai Dong	*Ophiopogon japonicus*	Root tuber	9
Gua Lou	*Trichosanthes kirilowii Maxim*	Mature fruit	9
Zhe Bei Mu	*Fritillaria thunbergii Miq*	Bulb	9
Mu Dan Pi	*Paeonia Suffruticosa Andrew*	Root bark	9
Zhi Yin Yang Huo	*Epimedium brevicornu Maxim*	Whole herb	6
Chao Bai Guo	*Ginkgo biloba L*	Mature seed	9
Chen Pi	*Citrus reticulata Blanco*	Peel of fruit	9
Zhi Gan Cao	*Glycyrrhiza uralensis Fisch*	Root and rhizome	9

At the same time, all the patients will also be treated with conventional modern medicine. Considering the side effects and costs, the application of pirfenidone and nintedanib will not be limited uniformly. During the whole procedure, all the patients will be visited every 13 weeks and receive given physical examinations. Blood and urine samples and exhaled breath condensate will be collected with the participants’ consent for further researches. If patients are under AE, the Chinese medicine granule or placebo will be suspended until the condition becomes stable. To improve the patients’ adherence, the remaining drugs and empty bags will also be returned except for regular telephone follow-up. The whole procedure for each patient is found in Fig. 2.

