#### Primary outcomes

##### Exacerbations of IPF

The frequencies of acute exacerbations of IPF, which is assessed by AEIPF-related hospitalization, is the primary outcome measure. AEIPF is characterized by significant respiratory deterioration, with an unknown cause within the past 1 month [28]. If the interval between any two AEIPF-related hospitalizations is less than 7 days, they are considered as one AE. The AE will be recorded at every visit, and the total number in the whole process (1-year treatment period) will be calculated. A higher number in a given period indicate the deterioration of IPF and a worse prognosis. A lower number in the experimental group will indicate better efficacy.

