##### Proportion of disease progression-free survivals

The endpoints of free disease progression in this study include any of the following events [29]: forced vital capacity (FVC) decreased by 10%, diffusing capacity percentage of the predicted value (DLCO%) by 15% compared to baseline, patient death, and lung transplantation. At the end of treatment, the proportion of the patients without any of the above endpoints will be calculated.

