##### All-cause mortality

Any death for IPF patients in this study with any cause will be recorded and counted. All-cause mortality will be calculated at the end of the treatment in each group. A lower number in the experimental group indicate a better efficacy for the intervention in improving prognosis.

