#### Safety outcomes

We will also evaluate the safety of interventions in this study. Safety outcome measures, including routine blood, urine, and stool tests; liver and kidney function tests; and electrocardiography, will be examined. Any adverse events will also be recorded and managed according to the degrees of damage at any time they occur during the treatment period. Then, we will also report to the ethics committee for further management. Based on our previous studies, the possible adverse events are transient gastrointestinal discomfort without the need for intervention.

Pulmonary function, routine blood, urine and stool tests, liver and kidney function tests, and electrocardiography will be tested and recorded at baseline (week 0), at 6 months after treatment (week 26), and at the end of the treatment (week 52). 6MWT, clinical symptoms and signs, MMRC, CAT, SF-36, SGRQ, and ATAQ-IPF will be completed and recorded at week 0, week 13, week 26, week 39, and week 52 in the process of trial.

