##### Data management and statistical analysis plan

Statistical analysis will be conducted both in the intent-to-treat (ITT) and pre-protocol (PP) data. ITT analysis will be applied to analyze the safety data. All the data from any included patients will be analyzed regardless of their withdrawal from the trial. The PP analysis will be adopted to assess the efficacy of the interventions. If data permit, sub-group analysis will also be performed to help clarify the therapeutic effect of interventions.

All the *P* values will be set as two-tailed with a significant level of 0.05. Measurement data will be shown with mean ± SD, median, and inter-quartile range. Count data will be presented by frequency or composition ratio. Analysis of variance (ANOVA) will be used to test for the differences in continuous variables, with the chi-square test for categorical variables. If necessary, the paired *t*-test will be applied to intra-group comparison data with normal distribution and homogeneous variance, and the Wilcoxon signed-rank sum test will be used for non-normal distribution or uneven variance. Repeated-measures ANOVA will be used to test the continuous response variables that are measured at more than two time points for the same patient, such as 6MWT, clinical symptoms and signs, mMRC, and HRQoL. To improve the quality of data, all the data management and statistical analysis will be conducted by the Jiangsu Famous Medical Technology Co., Ltd. in Nanjing, China.

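### Drop-out item (2) ends trial participation after allergy or a serious adverse event, where stopping study drug would be enough

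*Protocol article*

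**What the plan says.** Drop-out criteria has three items. Item (1) covers patients unwilling to go on. Item (2) covers those who "should not continue to participate in the trial due to allergy or serious adverse events". Item (3) covers those off medication and examinations and lost to visits.

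Eliminated criteria also withdraws patients for adherence below 80% or above 120% (item 1) and for stopping the drug themselves (item 3). Their existing records are kept.

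Acute exacerbations, which the article abbreviates as AE, have their own rule in Procedures and interventions: "If patients are under AE, the Chinese medicine granule or placebo will be suspended until the condition becomes stable".

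For the three primary outcomes and mortality:
- Exacerbation hospitalisations are recorded at visits, and "the total number in the whole process (1-year treatment period) will be calculated".
- 6MWD and the questionnaires "will be completed and recorded at week 0, week 13, week 26, week 39, and week 52 in the process of trial".
- Progression-free status is based on FVC, DLCO%, death and transplantation: "At the end of treatment, the proportion of the patients without any of the above endpoints will be calculated". Under Safety outcomes, lung function is measured at weeks 0, 26 and 52.
- For mortality, "Any death for IPF patients in this study with any cause will be recorded and counted".

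On analysis: "Statistical analysis will be conducted both in the intent-to-treat (ITT) and pre-protocol (PP) data". The same paragraph says that data are analysed whether or not a patient withdrew, ties ITT to the safety data, and assigns the assessment of efficacy to the per-protocol set.

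**The concern.** Item (2) treats two decisions as one: whether a patient should go on taking the granule, and whether the patient should go on being measured. A safety event settles the first but not the second. Because unwillingness and loss to visits are listed separately, the patients caught only by item (2) are those from whom data could still be obtained.

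These patients are selected by a serious event or an allergy. Those who leave after a serious event are likely to be sicker than those who stay, so the missing walk distances and lung function are unlikely to be missing at random. Two primary outcomes are exposed: 6MWD, which also sets the sample size, and progression-free status. Data that were never collected cannot be restored by any later analysis.

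**Working it through.** **1. What an exit under item (2) loses.** From the stated schedule (6MWD after baseline at weeks 13, 26, 39 and 52; FVC and DLCO% after baseline at weeks 26 and 52):

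| Exit | 6MWD visits lost | Lung function lost |
|---|---|---|
| before week 13 | 4 | weeks 26 and 52 |
| weeks 13 to 26 | 3 | weeks 26 and 52 |
| weeks 26 to 39 | 2 | week 52 |
| weeks 39 to 52 | 1 | week 52 |

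A patient who leaves before week 26 has no follow-up lung function, so progression by FVC or DLCO% cannot be judged. Death is a partial exception, since the mortality outcome records any death and makes no exception for drop-outs.

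**2. Whether other text recovers the loss.** Analysing data regardless of withdrawal covers data that exist, not visits that did not take place. Preserving the records of eliminated patients is likewise about existing records. The 13-weekly visits are stated for all patients, but a patient whose participation has ended is not clearly among them.

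**3. Whether the exacerbation rule conflicts.** The rule in Procedures and interventions is specific: suspend drug until stable, and the patient stays. Item (2) is general and rests on a judgement that someone should not continue. The article does not say whether an AEIPF hospitalisation is a serious adverse event. The two rules can both be followed; what is left open is how a centre handles an exacerbation that it also regards as a serious adverse event.

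**4. Whether rewording item (2) alone is enough.** It is not. If adherence is taken over the planned 52 weeks (an assumption; the article gives no denominator), 80% is 0.80 × 52 = 41.6 weeks. A patient who otherwise took every dose but stopped for safety before about week 42 would fall below 80% and be withdrawn under Eliminated criteria item (1). Item (3) could be applied too if the stop is recorded as the patient's own. The per-protocol efficacy analysis could then still leave the patient out.

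**5. The plan's own drop-out figure.** 124 / (1 − 0.20) = 155, against 156 stated, which agrees to within one patient. The allowance is 156 − 124 = 32 per group. It protects precision but does not correct for who leaves.

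**6. Illustration only; all inputs except 156 per arm and 31.81 m are assumed.** It models only exits that follow an exacerbation, the event for which the plan prescribes suspension, so it does not estimate the size of this point. Take a control rate L of 0.2 to 0.6 AEIPF per year, a true rate ratio of 0.60, and a share q of 10% or 25% of exacerbations ending participation. The share leaving is p = 1 − exp(−L·q), with 0.6·L in place of L for JHG.
- q = 10%: 2.0–5.8% of control and 1.2–3.5% of JHG leave. q = 25%: 4.9–13.9% and 3.0–8.6%.
- Observed AEIPF ratio, from counts (1 − exp(−L·q))/q: 0.602–0.607 and 0.606–0.618, so the counts lose little.
- 6MWD shrinkage = (p control − p JHG) × D, where leavers would walk D = 50 to 100 m less: 0.4–2.3 m and 1.0–5.3 m. Against 374.38 − 342.57 = 31.81 m this is 1–7% and 3–17%. The 17% needs every extreme at once.
- Progression-free difference among completers, (f − p·g)/(1 − p) per arm, with a true difference f of 10 points (50 v 60% or 60 v 70%) and g = 10 to 30% of leavers progression-free: 9.1–10.0 and 7.6–9.9 points. Recorded deaths reduce this distortion. In the worst case (60 v 70%, g = 10%, p = 13.9% and 8.6%), if half the leavers are known deaths, (f − p·g)/(1 − p/2) gives a difference of about 9.2 instead of 7.6 points.

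**The case against.** The strongest reply is that item (2) calls for judgement: it describes patients who should not continue, and Safety outcomes has adverse events managed by degree of harm. Not every serious event forces an exit. That stands, and it limits how many patients are affected. It does not change what happens to those judged unfit: by the wording, they leave the trial.

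A second reply is that a condensed article may leave follow-up after withdrawal to the full protocol or to the standard operating procedures it mentions. That also stands, so the absence of stated follow-up is not the point here. The point is the stated rule. If the full protocol does continue visits for these patients, the published criterion is worded wrongly and still needs correcting.

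A reader might infer that item (2) and the exacerbation rule contradict each other, so that the first AEIPF hospitalisation ends counting of a primary outcome. The documents do not support this. The exacerbation rule keeps such patients in the trial, nothing classes an AEIPF hospitalisation as a serious adverse event, and even in the illustration the AEIPF ratio hardly moves.

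A reader might also infer a bias toward no difference. That follows only if exits come after exacerbations and JHG reduces them. For allergy and other serious adverse events, which item (2) names directly, the direction is unknown.

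**Conclusion.** The point holds as a badly fixed rule. Item (2) ends participation where ending study drug would do, and followed as written it discards remaining 6MWD visits and week-26 or week-52 FVC and DLCO% in patients selected by illness or allergy. The article gives no rates of serious adverse events, allergy or resulting exits, so neither the size nor the direction of any bias can be determined. The figures in the illustration rest on assumed rates and on the route least supported by the text, and should not be cited as an estimate. The overlap with the exacerbation rule is a matter for clarification. The change is worth making because it is simple and unrecorded data cannot be recovered later.

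**What to change.** Make four linked changes:
1. Reword item (2) so that allergy or a serious adverse event ends study drug only. Add that an AEIPF hospitalisation is an outcome, handled by suspending drug, and is not in itself a reason for drop-out.
2. State that these patients are not withdrawn from follow-up under Eliminated criteria items (1) or (3) because of the resulting low adherence or stopping of drug.
3. With the patient's consent, continue the scheduled visits and the recording of AEIPF hospitalisations and vital status to week 52. Unwillingness under Drop-out item (1) still ends participation.
4. Include these data in an ITT efficacy analysis reported beside the per-protocol analysis.

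The cost is a few sentences, a protocol revision submitted to the ethics committee (as the ethics section requires) and a note to the 11 centres. The visits are already scheduled and ITT is already named. Each such patient adds at most four off-treatment visits, and some will be too ill to walk, so not every 6MWD value will be recovered. At manuscript submission 70 of 312 patients were enrolled; how many would still benefit depends on when the change is made.
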